### Statistical analysis.

An independent statistician will carry out the statistical analysis. He or she will have no knowledge of whether each participant belongs to one group or another, nor what type of treatment was implemented in each group. All necessary data will be extracted into an Excel spreadsheet and analysed using IBM® SPSS® Statistics 27.0.1.0.

A Kolmogorov-Smirnov test will be used to check whether or not the data fit a normal distribution. A descriptive analysis will be carried out to explore the variables related to the study.

Quantitative variables with parametric distribution will be assessed with a T-test or ANOVA, while if the distribution is non-parametric a Mann-Whitney test will be used. This analysis will examine whether there are differences between groups that may support or refute the hypothesis that strength training reduces hospital stay, ICU stay and/or complications in this type of patient. This analysis will also be used to test whether ventilation and respiration values as well as quality of life values are different in each group.

To assess whether there is an influence of confounding variables (BMI, toxic habits, comorbidities, underlying pathologies) on the direction of the dependent variables, multiple regression will be performed.

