#### Sample size.

For the primary outcome (time in the intensive care unit), an effect size of 0.613 was determined based on previous research on the effect of a multidimensional preoperative intervention in patients awaiting elective coronary artery bypass graft surgery (47). To obtain a statistical power of 0.8 with a 2-tailed alpha of 0.05 in a Student's t-test, considering a dropout rate of 10%, a total of 96 participants (48 subjects per group) were required.

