## **RESULTS**

The results will first be expressed taking into account hospital and/or ICU stay as the primary variable. Also, to address secondary variables with criteria, values related to postoperative complications and quality of life will be cited. This will be followed by values related to functionality and muscular and aerobic endurance. Finally, it will be reflected whether confounding variables may interfere with the direction of dependent variables.

Quantitative variables will be expressed in terms of means and standard deviations, provided that they comply with a parametric distribution, or in medians and interquartile ranges if this is not the case. Box and whisker plots shall be used for their graphical representation.

Categorical variables, corresponding to the EuroQoL-5D items, will be expressed in terms of frequency and percentages and bar charts will be used for ordinal variables, while nominal descriptive variables will be expressed using pie charts.

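### A normality pre-test decides whether ICU stay is compared by means or by ranks, so the primary effect measure is not fixed in advance

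*Protocol*

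**What the plan says.** The Statistical analysis section of the Protocol sets a two-step rule. First, "A Kolmogorov-Smirnov test will be used to check whether or not the data fit a normal distribution". Then: "Quantitative variables with parametric distribution will be assessed with a T-test or ANOVA, while if the distribution is non-parametric a Mann-Whitney test will be used". The same section says this analysis will "support or refute the hypothesis that strength training reduces hospital stay, ICU stay and/or complications in this type of patient", so the rule covers ICU stay and hospital stay, and no outcome is exempted. A multiple regression for confounders follows, with no scale stated.

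The RESULTS section ties the summary to the same condition: means and standard deviations "provided that they comply with a parametric distribution, or in medians and interquartile ranges if this is not the case".

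The Sample size section identifies the primary outcome and its planning effect: "For the primary outcome (time in the intensive care unit), an effect size of 0.613 was determined". It then computes the sample size for a two-sided 5% comparison "in a Student's t-test" and mentions no other test.

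The Variables section defines three stay outcomes (ICU, ward and total), recorded to the minute. The Protocol gives no significance level for the pre-test. It does not say whether the pre-test is run per arm or pooled, or whether it is corrected for an estimated mean and SD.

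**The concern.** A t-test compares mean hours. Mann-Whitney compares the chance that a patient in one arm has a shorter stay than a patient in the other. These are different quantities, and here the choice between them is made after the data are in. Three things follow.

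- The comparison that carries the primary conclusion may not be the one the trial was sized for, and the rank branch gives no estimate on the scale of the 0.613.
- ICU, ward and total stay can each take a different branch, although total stay is the sum of the other two.
- The regression belongs to neither branch, so adjusted and unadjusted results may be on different scales.

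The pre-test is also unnecessary here. Stay is a positive time and probably right-skewed, so a suitable scale can be chosen before any data are seen. This is not a detail left to a later analysis plan: the Protocol states the decision rule, and a plan that followed it would inherit the problem.

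**Working it through.** **1. The planned sample size.** Inputs from the Sample size section: effect 0.613, power 0.80, two-sided alpha 0.05, dropout 10%. The normal approximation gives 2 × (1.960 + 0.842)² / 0.613² = 41.8, so 42 per arm. The exact t-test calculation gives 42.76, so 43 per arm. Then 43 / 0.90 = 47.8, so 48 per arm and 96 in total. The stated figure reproduces, and 43 evaluable patients per arm give a t-test power of 0.802.

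**2. The branches measure different things.** Take log-normal stays with a shift of 0.613 log-SDs. The Mann-Whitney probability is Φ(0.613 / √2) = Φ(0.433) = 0.67, whatever the spread. The ratio of means is exp(−0.613 × log-SD): 0.78 at log-SD 0.4 and 0.54 at log-SD 1.0. One rank effect thus corresponds to very different effects on mean stay.

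**3. Effect of the pre-test, with 0.613 as a standardised difference in mean hours.** The documents give no SD or shape for ICU stay, so the distributions are assumed. Settings: 43 per arm; Lilliefors-corrected Kolmogorov-Smirnov test in each arm at 5%; Mann-Whitney if either arm rejects, otherwise Student's t; 4,000 trials per setting. The share sent to Mann-Whitney is taken from the runs with a true effect.

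| Data | Sent to Mann-Whitney | Type I error, two-stage | Power: t | Power: Mann-Whitney | Power: two-stage | t and Mann-Whitney disagree |
|---|---|---|---|---|---|---|
| Normal | 9.2% | 0.043 | 0.790 | 0.769 | 0.785 | 5.2% |
| Log-SD 0.2 | 30.0% | 0.056 | 0.808 | 0.802 | 0.810 | 6.5% |
| Log-SD 0.3 | 50.1% | 0.050 | 0.804 | 0.802 | 0.805 | 6.6% |
| Log-SD 0.4 | 72.7% | 0.051 | 0.797 | 0.816 | 0.815 | 8.7% |
| Log-SD 0.6 | 94.7% | 0.048 | 0.834 | 0.870 | 0.870 | 9.5% |
| Log-SD 0.8 | 99.6% | 0.048 | 0.863 | 0.937 | 0.937 | 10.0% |

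The simulation error of a 5% rate is √(0.05 × 0.95 / 4,000) = 0.0034. The largest type I error, 0.056, lies (0.056 − 0.050) / 0.0034 = 1.8 standard errors above 0.05, which shows no material inflation.

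**4. The same check with 0.613 on the log scale.** The first two columns show how often normality is accepted in both arms, so that the t-test is used. The last two show how often the final verdict differs from always using Mann-Whitney (6,000 trials per setting).

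| Log-SD | Accepted, corrected | Accepted, uncorrected | Verdict changed, corrected | Verdict changed, uncorrected |
|---|---|---|---|---|
| 0.4 | 28% | 94% | 1.6% | 7.8% |
| 0.6 | 5% | 68% to 72% | 0.2% | 6.9% |
| 0.8 | 0.5% | 31% to 33% | 0.1% | 3.5% |
| 1.0 | under 0.1% | 11% | 0% | 0.9% |

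Ranges come from two separate runs. Over log-SD 0.2 to 1.0, the verdict changes in about 0% to 4% of trials (corrected) and 1% to 8% (uncorrected). Two-stage power is 0.77 to 0.80, within about 2 points of fixed Mann-Whitney and up to 3 points below a t-test on log hours. Type I error is about 0.04 to 0.06.

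**5. Reading the results.** The variant of the pre-test, which the Protocol does not name, largely decides which analysis is run: at log-SD 0.6 the t-test is used in 5% of trials or in about 70%. Error rates and power hardly move. What moves is the quantity being estimated.

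**The case against.** The best defence is that the rule does little damage. Type I error holds, power is close to that of a fixed test, and in the skewed settings of step 3 the rule beats a fixed t-test on raw hours (at log-SD 0.8, 0.937 against 0.863). The analyst is to be unaware of group and treatment, which leaves little room to choose a favourable test. Sizing on a t-test suggests an intended default, and the regression is there to examine confounding, so a mismatch of scale in it is minor. All of this stands. It limits the size of the point, but none of it says which effect the trial will report.

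A reader might infer more than the documents support:

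- **That the conclusion often turns on the pre-test.** With the effect on the log scale, t and Mann-Whitney disagree on significance in 9% to 22% of simulated trials at log-SD 0.4 to 1.0. That compares two fixed tests. Where disagreement is greatest, the pre-test nearly always selects Mann-Whitney, so the verdict changes far less often.
- **That power falls to 0.62.** That figure is for a raw-hours t-test used in every trial at log-SD 1.0, where even the uncorrected pre-test lets the t-test through in only about 11% of trials.
- **That a log-scale analysis is the only remedy.** The Sample size section does not place 0.613 on the log scale, and mean hours is a legitimate target.

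**Conclusion.** The point holds as one of prespecification. The Protocol lets a test on the trial's own data choose the primary effect measure and its summary, and the result may not be the comparison behind the sample size. The three stay outcomes may also be analysed by different methods.

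The consequence for error rates is small: type I error near 5%, power at most about 3 points below the best fixed test considered, and a changed verdict against fixed Mann-Whitney in about 0% to 4% (corrected) or 1% to 8% (uncorrected) of trials. These figures rest on assumed log-normal stays, 43 evaluable patients per arm and a pre-test in each arm at 5%. The structural point rests on the text alone. Neither inflated type I error nor a wrong sample size follows from it. The rule should be changed before analysis, but it does not by itself invalidate the trial.

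**What to change.** Delete the normality pre-test for the stay outcomes. Before analysis, name one effect measure and one test for ICU stay, and use the same scale for ward stay, total stay and the multiple regression. Either of these would do:

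- a t-test or linear regression on log hours, reported as a ratio of geometric means with a 95% confidence interval, which suits positive and probably skewed times;
- a difference in mean hours with a Welch or bootstrap interval, which stays closest to the present sizing.

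Keep Mann-Whitney as a sensitivity analysis, and report both mean (SD) and median (IQR) in each arm whatever the distribution looks like.

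The change is to wording and needs no extra data. If the log scale is chosen, results are ratios rather than hours, and the Protocol must state that 0.613 is assumed to apply on that scale. If a rank test were made primary instead, it would need its own sizing basis. For normal data, 42.76 / 0.955 = 44.8, so 45 evaluable per arm, and 45 / 0.90 = 50 per arm, or 100 in total.

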### Participants: eligibility and recruitment.

Ninety-six patients will participate in this study, whose recruitment is expected to take place between June 2023 and July 2025. The inclusion criteria for the sample will be: adult patients diagnosed with valvular pathology who have been admitted as candidates for cardiac surgery for the first time, and whose appointment for intervention has been scheduled. Only those who voluntarily agree to participate in the study and sign the informed consent form will be admitted. Patients with the following characteristics will be excluded: stage 4 or 5 renal failure, low ejection fraction, Euroscore greater than 15, non-ST-segment elevation acute coronary syndrome (NSTEMI) and coronary artery disease or need for urgent intervention.

Those with cognitive deficit, diagnosis of pulmonary disease, heart failure, unstable angina, arrhythmias, severe aortic stenosis, mitral regurgitation, aortic aneurysm, recent embolism, recent myocarditis or pericarditis, or comorbidities limiting the performance of the functional test will also be excluded.

All persons referred to the Physiotherapy Unit from the Cardiac Surgery Unit of the Hospital de La Ribera (Alzira, Spain) will be considered candidates for this study, as long as they attend the initial physiotherapy assessment. Recruitment will therefore be carried out among these attendees and eligibility will be confirmed by a physiotherapist. Signed informed consent will be collected prior to any measurement or intervention.

The assignment of each participant to one group or another is not the responsibility of the researchers, but will be randomised. The initial and final evaluation will be carried out by three physiotherapists who will act without knowing the assignment of each participant to one or the other group. The physiotherapists who carry out the measurements will attend a training session to unify the measurement criteria for each variable.

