| Tool     | Accounting of the days according to the data reflected in the medical history.                                                                                                                | EuroQoL-5D questionnaire                                      | 
 
• Sibelmel Datospir Peak-10.
 
• Portex Coach 2 Incentive Spirometer 4000ml.
 
• MicroRPM device (Carefusion)
 
                       | 
 
• 2 minute step test
 
• Short Physical Performance Battery.
 
• Activity logging via Google Fit
 
• Hand dynamometry.
 
• Dynamometer Lafayette
 
 |
| Time     | At hospital discharge                                                                                                                                                                         | Pre-surgery and 6 months after discharge.                     | Pre-surgery, 24h after the surgery, at the hospital discharge                                                                                                                                       | Pre-surgery, 24h after the surgery, at the hospital discharge                                                                                                                                                                  |

1. Hospital stay. Hospital stay will be measured in hours and minutes, so that stays of less than 24 hours can be better accounted for. Three different variables will be recorded:
  - Intensive Care Unit stay: counted from the end of the surgical procedure until transfer to the ward.
  - Ward stay: counted from transfer to ward until discharge from hospital.
  - Hospital stay: counted from the end of the surgical procedure until discharge from hospital.

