2. Quality of life. Perception of quality of life will be recorded and assessed both before and six months after surgery. The EuroQOL-5D quality of life questionnaire, valid and reliable for analysing quality of life in this type of patient, will be used. The participant assesses their capacity for self-care, mobility, activities of daily living, the presence of pain or anxiety/depression in categorical levels of severity (no problems, some problems or moderate problems and severe problems) and their perception of health using a visual analogue scale. (34). As there are no published data on the inter-examiner reliability of this tool (35) a single nurse will be responsible for collecting these values.
3. Respiratory values. Respiratory values shall be collected on three different occasions: before surgery, immediately after surgery and on the day of hospital discharge. These tests shall be repeated until three acceptable measurements are obtained (difference <10%), with a one-minute rest between them, and the highest value shall be recorded (36,37). Three measurements shall be made of:

- **Inspiratory capacity:** This is defined as the volume of air that can be inspired from the resting inspiratory position. With the patient in a seated position, the Portex® Coach 2® 4000 ml incentive spirometer will be used to measure inspiratory capacity and the value of the variable will be expressed in millilitres. The patient will be instructed to take a deep, unforced inspiration, trying not to exceed the flow mark (38).
  - **Peak expiratory flow:** This is defined as the maximum flow a person is able to exhale during a brief maximal expiratory effort after a full inspiration. With the patient in a seated position, the Sibelmed® Datospir Peak-10 device will be used to record the peak expiratory flow and the value of the variable will be expressed in litres/second. The patient will be instructed in a maximal forced expiration, preceded by a deep nasal inspiration up to inspiratory reserve volume (39).

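### Secondary outcomes measured before and after surgery are compared without using the patient's own starting value, and the respiratory and quality-of-life visit times conflict

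*Protocol*

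**What the plan says.** Under Variables, the protocol measures respiratory values and exercise capacity (including strength) once before surgery and twice after it. Quality of life (EQ-5D) is measured once before and once after.

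Under Statistical analysis, quantitative variables go to a t-test or ANOVA if normally distributed and to Mann-Whitney otherwise. The section adds: "This analysis will also be used to test whether ventilation and respiration values as well as quality of life values are different" between the groups. Strength and exercise capacity are not named in that sentence and fall under the general rule for quantitative variables. A separate multiple regression examines body mass index, toxic habits, comorbidities and underlying pathologies. No analysis in the section uses the outcome's own pre-operative value.

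The measurement times are given more than once:

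- Respiratory values, Time row of the variables table: "Pre-surgery, 24h after the surgery, at the hospital discharge".
- Respiratory values, numbered text: "before surgery, immediately after surgery and on the day of hospital discharge".
- Quality of life, Time row of the table: "Pre-surgery and 6 months after discharge".
- Quality of life, numbered text: "Perception of quality of life will be recorded and assessed both before and six months after surgery". The Outcomes row of the same table also counts from surgery.

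For exercise capacity, table and text agree: before surgery, 24 hours after it, and at discharge.

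**The concern.** A patient's starting value usually predicts the later value of the same measure. A test on follow-up values alone leaves that predictable part in the error term. Mann-Whitney cannot take a covariate at all. The effect on ventilatory variables is the declared secondary objective, and the sample size was set for ICU time only, so what the trial can say on these outcomes depends on how efficiently they are analysed.

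The timing conflicts raise a different problem. A measurement immediately after cardiac surgery and one at 24 hours are not the same assessment, and the protocol does not settle which is meant. A six-month assessment counted from discharge falls at a date that depends on length of stay, which the intervention is meant to change.

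The term pre-surgery is also undefined. The programme fills the three weeks before surgery, so a pre-surgery value could come before or after it. Only a value from before the programme is a true baseline.

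**Working it through.** **1. The plan's own figure.** Sample size rests on "an effect size of 0.613 was determined based on previous research" and "a statistical power of 0.8 with a 2-tailed alpha of 0.05", with 10% dropout. A two-sample t-test by the noncentral t distribution needs 42.76, so 43 per group. Then 43 / 0.90 = 47.8, so 48 per group and 96 in total. The stated 96 is reproduced. ICU time has no baseline value, so nothing below changes it.

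**2. What adjustment gains.** Let r be the correlation between the baseline and follow-up values of an outcome. ANCOVA on a true baseline multiplies the residual variance by 1 − r². This is equivalent to multiplying the number of patients by 1 / (1 − r²), and it raises a standardised effect d to d / √(1 − r²).

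Inputs: 43 evaluable per arm (step 1); two-sided alpha 0.05; d = 0.4, an illustrative value that is not in the documents; r assumed from 0.3 to 0.8, because the documents give none. Power is that of a two-sample t-test at the raised effect, ignoring the one degree of freedom spent on the covariate.

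| r | 1 − r² | Patient multiplier | 0.4 / √(1 − r²) | Power |
|---|---|---|---|---|
| none used | 1.00 | 1.0 | 0.400 | 45% |
| 0.3 | 0.91 | 1.1 | 0.419 | 48% |
| 0.5 | 0.75 | 1.3 | 0.462 | 56% |
| 0.6 | 0.64 | 1.6 | 0.500 | 63% |
| 0.7 | 0.51 | 2.0 | 0.560 | 73% |
| 0.8 | 0.36 | 2.8 | 0.667 | 86% |

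The smallest effect detectable with 80% power at 43 per arm is 0.61 SD unadjusted. With adjustment it is 0.61 × √(1 − r²): 0.58 at r = 0.3, 0.53 at 0.5, 0.44 at 0.7 and 0.37 at 0.8.

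**3. Whether the baseline exists.** Under Participants, candidates attend an initial physiotherapy assessment, an initial and a final evaluation are planned, and "Signed informed consent will be collected prior to any measurement or intervention". That sentence places consent before both measurement and intervention; it does not place measurement before intervention. Neither evaluation is linked to the pre-surgery time in the variables table. A pre-programme value is therefore plausible but not established.

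**4. Timing, side by side.**

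| Outcome | Table, Time row | Numbered text | Agree? |
|---|---|---|---|
| Respiratory, first postoperative test | 24 h after surgery | immediately after surgery | No |
| Respiratory, last test | discharge | day of discharge | Yes |
| Quality of life, follow-up | 6 months from discharge | 6 months from surgery | No |
| Exercise capacity and strength | 24 h and discharge | 24 h and discharge | Yes |

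**The case against.** The strongest reply is that this is about efficiency, not error. If allocation is random, as Participants states, an unadjusted comparison is valid, and chance baseline imbalance is already reflected in its standard error and type I error rate. That stands: a reader might infer that the planned tests are invalid or biased, and the documents do not support it. They also do not support reading the sample size as too small, since N rests on ICU time.

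A second reply is that covariate detail belongs in a SAP, which is not shown, and that ANOVA is named without its form. This carries less weight. The protocol does more than stay silent: it names the tests and lists the regression covariates, and the list omits the most useful one.

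A third reply is that the gain may be small. This also stands. With no correlation in the documents, a reader might take a doubling of the effective sample as established. That needs r of about 0.7, and nothing shows that one value of r holds at 24 hours, at discharge and at six months alike. At r = 0.3 the gain is three or four points of power.

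On timing, a reader might extend the contradiction to strength and exercise capacity, but those times agree. Nor does any passage propose pooling immediate and 24-hour respiratory values; the two descriptions appear to concern one visit. The two quality-of-life anchors differ only by the postoperative stay, which is short against six months.

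**Conclusion.** The point holds as a worthwhile improvement to the secondary analyses, together with two plain timing contradictions.

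The named comparisons do not use the outcome's own starting value. Adjusting for it costs almost nothing if a pre-programme value is collected. For a 0.4 SD effect and 43 evaluable patients per arm, the gain runs from slight (45% to 48% power at r = 0.3) to large (45% to 86% at r = 0.8). Its size cannot be fixed from the documents.

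The conclusion rests on three conditions: random allocation, a baseline taken before the programme, and a roughly continuous outcome. The first needs confirming, because the Design section describes the trial as non-randomised and then as randomly assigned. The second is not established by the protocol. The third fails for the three-level EQ-5D items and the categorised parts of the Short Physical Performance Battery.

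The first postoperative respiratory time and the quality-of-life anchor are each stated in two incompatible ways and need reconciling whatever analysis is chosen.

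**What to change.** 1. Under Variables, state for each outcome whether the pre-surgery value is the initial assessment described under Participants, taken before the three-week programme.
2. Under Statistical analysis, where that value exists, analyse the continuous outcomes by ANCOVA with it as covariate. These are maximum inspiratory and expiratory pressure, peak expiratory flow, inspiratory capacity, step count, grip strength, biceps and quadriceps dynamometry, and the EQ-5D visual analogue scale. A mixed model is an alternative where there are two postoperative visits, which excludes quality of life. Report the adjusted difference with its 95% confidence interval.
3. Do not adjust for a value taken after the programme: it follows allocation, and adjusting for it could remove part of the training effect.
4. Use an ordinal method for the EQ-5D items and the categorised Short Physical Performance Battery parts.
5. Reconcile the first postoperative respiratory time between table and text, keeping the discharge visit.
6. Use one anchor for the six-month quality-of-life assessment. Surgery is preferable, because a discharge anchor moves with length of stay.

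The cost is wording only if the initial assessment already records these outcomes. If it does not, each missing outcome needs one added pre-programme measurement, or its comparison stays unadjusted. The sample size does not change.

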#### Data collection

Sex, age, underlying pathology, comorbidities, body mass index (BMI) and toxic habits will be the descriptive variables collected in both groups. All these data will be stored in their clinical history and will be extracted by the person in charge of epidemiological data management at the hospital, who will include them in an Excel table, also indicating whether each participant survives or not, as well as the information related to the intervention and the pathology, catalogued using the International Classification of Diseases 11 (ICD-11) or the appropriate one if there are updates. Days of hospitalisation, intensive care unit (ICU) stay, if applicable, Charlson comorbidity index, and possible postoperative complications for each participant will also be reflected in this table.

Although the database from which the data will be extracted will not contain personal data, as each participant will receive a numerical identification code, all researchers will sign a data confidentiality commitment sheet prior to the start of the study, which states that patients' personal data will be protected.

The medical information of each participant and his or her evolution at each point of the measurement shall be recorded in his or her medical record.

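### A EuroSCORE is required of every participant at entry but is neither named for extraction nor used as a covariate, so precision for the ICU-stay comparison is given up

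*Protocol*

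**What the plan says.** **Eligibility.** The protocol's section on participants, eligibility and recruitment excludes patients with a "Euroscore greater than 15". The score is mentioned nowhere else, and neither its version nor its scale is stated.

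**Extraction.** The Data collection section states: "Sex, age, underlying pathology, comorbidities, body mass index (BMI) and toxic habits will be the descriptive variables collected in both groups". It adds survival, coded information on the intervention and the pathology, and lengths of stay. It closes the list with "Charlson comorbidity index, and possible postoperative complications for each participant will also be reflected in this table". The EuroSCORE is not named.

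**Analysis.** The Sample size section reads "For the primary outcome (time in the intensive care unit" and sizes the trial on a Student's t-test. For the group comparison, the Statistical analysis section says "Quantitative variables with parametric distribution will be assessed with a T-test or ANOVA", and "if the distribution is non-parametric a Mann-Whitney test will be used". No covariate is attached to either. A separate multiple regression is planned to see whether confounders have an influence, and its listed covariates are "confounding variables (BMI, toxic habits, comorbidities, underlying pathologies". The EuroSCORE is not among them. Neither are age and sex, although both are collected.

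**The concern.** A score that decides entry has to be obtained for each patient before allocation. It is therefore a baseline measure of surgical risk that costs nothing more to use. The primary outcome is time in intensive care after cardiac surgery, for which such a score is a natural candidate covariate. The protocol names both the extracted variables and the regression covariates, and the score is in neither list. This is a stated choice, not a detail left open for a later plan.

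Precision is at stake. The sample size leaves almost no power in reserve, and a prognostic baseline covariate is a way to gain some without recruiting more patients. The planned regression reaches surgical risk only indirectly, through open-ended lists of comorbidities and pathologies.

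**Working it through.** **Inputs from the protocol (Sample size section):** standardised effect d = 0.613; two-sided alpha 0.05; power 0.80; dropout 10%; 96 patients, 48 per group; Student's t-test.

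**Input not in the protocol:** R², the share of variance in ICU stay explained by the EuroSCORE. No figure is given, so 0 to 0.30 is assumed.

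**Step 1: reproduce the stated size.** A two-sample t-test (noncentral t) with these inputs needs 42.76 per arm, rounded up to 43. With dropout, 43 / 0.90 = 47.8, rounded up to 48 per arm, or 96 in total. This matches the protocol. Power at 43 evaluable per arm is 80.2%.

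**Step 2: add one baseline covariate.** The residual SD is multiplied by sqrt(1 − R²), so the effective effect size is 0.613 / sqrt(1 − R²). The one degree of freedom used is ignored. The last column is the total for 80% power, with 10% dropout added per arm.

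| Assumed R² | Effective d | Power at 43 per arm | Reduction in standard error | Total N for 80% power |
|---|---|---|---|---|
| 0 | 0.613 | 80.2% | 0% | 96 |
| 0.05 | 0.629 | 82.2% | 2.5% | 92 |
| 0.10 | 0.646 | 84.2% | 5.1% | 88 |
| 0.20 | 0.685 | 88.1% | 10.6% | 78 |
| 0.30 | 0.733 | 91.9% | 16.3% | 70 |

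Example at R² = 0.10: 0.613 / sqrt(0.90) = 0.646, which needs 39 per arm; 39 / 0.90 = 43.3, rounded up to 44, or 88 in total.

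**Step 3: chance imbalance between arms.** The standard error of the difference in mean score, in SD units, is sqrt(2/43) = 0.216.
- The 95% limit is 1.96 × 0.216 = 0.42 SD. The expected absolute difference is 0.80 × 0.216 = 0.17 SD.
- The shift this causes in the unadjusted estimate is the imbalance times sqrt(R²). At the expected imbalance it is 0.17 × 0.316 = 0.05 SD for R² = 0.10 and 0.17 × 0.447 = 0.08 SD for R² = 0.20. That is about 9% and 13% of 0.613.
- The unadjusted standard error already contains this variation. Adjustment narrows the 95% half-width of the effect from 0.42 SD to 0.42 × sqrt(0.90) = 0.40 SD, or 0.42 × sqrt(0.80) = 0.38 SD. This is the gain in Step 2 seen another way, not an additional one.

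All figures assume a normally distributed outcome, as the protocol's own calculation does.

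**The case against.** The strongest reply is that nothing here is invalid. Under random assignment an unadjusted t-test is a proper primary test, the trial was sized for it, and the 96 reproduces. A covariate is an optional gain, and the protocol already plans a regression that picks up part of the risk through comorbidities and pathologies. All of that stands.

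The size of the gain is also open to challenge. No document links the EuroSCORE to ICU stay, so R² could be near zero. The cut-off at 15, together with exclusions such as low ejection fraction, advanced renal failure and urgent intervention, plausibly makes participants more alike in risk. Beside the listed covariates, only the score's additional share of variance counts. The lower end of the range is therefore the likelier one, and at R² of 0.05 to 0.10 the gain is 2 to 4 points of power.

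Three stronger readings are tempting but unsupported:
- **That adjustment could never be made later.** The Data collection section keeps each participant's medical information in the medical record and gives each an identification code. Its wording on intervention and pathology data might even be read to cover the score. The score is not named for extraction, but it is not shown to be lost.
- **That the omission distorts the result by 22 to 31% of the assumed effect.** That follows from putting the 95% limit of 0.42 SD into Step 3 at R² of 0.10 to 0.20. It describes an extreme draw, and the variation is already inside the standard error and the type I error.
- **That the comparison is confounded.** This would follow only if allocation were not random. The Design section uses both descriptions, but the section on participants says assignment is randomised. That contradiction needs its own resolution.

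**Conclusion.** The point holds as a missed gain in precision, not as an error in the test or the sample size. Every participant must have a EuroSCORE, yet the protocol does not name it for extraction, does not adjust the primary ICU-stay comparison for it, and omits it from the regression list. Under an assumed R² of 0 to 0.30, power at 43 evaluable per arm would be about 80% to 92%, with the lower part of that range more likely. The conclusion rests on random assignment, on an R² that the protocol does not supply, and on normal-theory calculations. With R² = 0 there is no gain, and the cost is one degree of freedom.

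**What to change.** - **Data collection section:** add the EuroSCORE obtained at screening to the extracted table, stating its version and scale.
- **Statistical analysis section, primary comparison:** pre-specify that the arm difference in ICU stay comes from a linear model with the EuroSCORE as a continuous covariate. State in advance that log-transformed stay or a rank-based ANCOVA will be used if stay is skewed. The planned fallback, Mann-Whitney, takes no covariate, so without this the adjustment would be dropped for skewed data.
- **Statistical analysis section, secondary regression:** represent comorbidity by the "Charlson comorbidity index", which is already collected, instead of an open list. Keep underlying pathology as a separate covariate, since it is a planned adjustment and there is no reason to drop it.
- **Sample size:** keep 96 and treat any gain as a reserve of power.

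The cost is one column taken from the screening record and a few sentences of text, with no new measurement and no extra patients.
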